## Abstract

**Background:**

In France, for patients aged 75 or older, it has been estimated that the hospital readmission rate within 30 days is 14 %, a quarter being avoidable. Some evidence suggests that interventions “bridging” the transition from hospital to home and involving a designated professional (usually nurses) are the most effective in reducing the risk of readmission, but the level of evidence of current studies is low. Our study aims to assess the impact of a care transition program from hospital to home for elderly admitted to short-stay units.

**Methods:**

This is a multicentre, stepped-wedge cluster randomised trial.

The program will be implemented at three times of the transition: 1) during the patient’s stay in hospital: development of a discharge plan, creation of a transitional care file, and notification of the primary care physician about inpatient care and hospital discharge by the transition nurse; 2) on the day of discharge: meeting between the transition nurse and the patient to review the follow-up recommendations; and 3) for 4 weeks after discharge: follow-up by the transition nurse.

The primary outcome is the 30-day unscheduled hospital readmission or emergency visit rate after the index hospital discharge.

The patients enrolled will be aged 75 or older, hospitalized in an acute care geriatric unit, and at risk of hospital readmission or an emergency visit after returning home.

In all, 630 patients will be included over a 14-month period. Data analysis will be blinded to allocation, but due to the nature of the intervention, physicians and patients will not be blinded.

**Discussion:**

Our study makes it possible to evaluate the specific effect of a bridging intervention involving a designated professional intervening before, during, and after hospital discharge.

The strengths of the study design are methodological and practical. It permits the estimation of the intervention effect using between- and within-cluster comparisons; the study of the fluctuations in unscheduled hospital readmission or emergency visit rates; the participation of all clusters in the intervention condition; the implementation of the intervention in each cluster successively.

**Trial Registration:**

This study has been registered as a cRCT at clinicaltrials.gov (identifier: NCT02421133). Registered 9 March 2015.

## Background

In France in 2010, 33 % of subjects aged 75 years or older were hospitalised at least once in a short-stay care unit [1]. The rate of unscheduled hospital readmissions within 30 days has been reported to reach 14 % for such patients (IC 95 % [12,0–16,7]), with nearly one quarter of these readmissions being preventable [2, 3]. There are numerous reasons for these readmissions: those linked to the patient (comorbidities, polypharmacy, functional disabilities, malnutrition, and musculoskeletal, psychocognitive and sensory disorders), to his environment (social isolation, absence of a care network, unsuitable home), and to the health care system (care during the hospital stay, hospital-to-home transition including management of patient discharge, and patient follow-up after discharge) [4].

Several literature reviews have attempted to identify effective interventions for managing the hospital-to-home transition [5–8]. Such interventions “aim, during and after hospitalisation, to prevent a breakdown in the continuity of care and to reduce the occurrence of adverse health effects, including preventable readmissions [5].” It was concluded that, in order to be effective, such interventions must combine several actions at three steps of the transition: 1) before the patient leaves the hospital, 2) at the time of discharge, and 3) within 48 h and up to 30 days after discharge. A decrease in readmissions within 30 days is the most frequently used criterion for evaluating the quality of in-hospital care and of the hospital-to-home transition. The implementation of an intervention program requires the identification of patients at risk of hospital readmission. Finally, it must be possible to adapt the intervention to each situation according to the specific needs of the patient and those supporting him.

Three-step transition interventions (i.e., bridging interventions) involving a specially assigned professional appear to be the most effective in reducing the risk of hospital readmission, but the level of evidence of current studies remains weak [5–7]: there have been few randomised controlled trials or multicentre studies, and the tested interventions have been heterogeneous in terms of the choice of the transition professional (generally nurses), the definition of the population at risk for readmission that is targeted by the intervention, and the follow-up time after hospitalisation [7]. In addition, the existing data do not permit the assessment of medico-economic impact [9].

### Objective

This study aims to assess the impact of a care transition program from hospital to home on the 30-day unscheduled hospital readmission or emergency visit rate after the index hospital discharge, for people aged 75 years or older who are admitted to short-stay care units.

The other objectives are to evaluate the impact of this transition program on the safety and quality of home-based care (mortality, quality of life, and patient satisfaction); to evaluate the implementation of the program (time required to set up the help scheme, and timing and frequency of communication among the various actors); and to carry out a medico-economic assessment including a cost-effectiveness analysis at 30 days and a budgetary impact study at 12 months.

## Methods/design

### Setting

The study is to take place in nine short-stay geriatrics units in hospitals across the Rhône-Alpes region of France (two university teaching hospitals, one private hospital, and five public hospitals) over a period of 14 months.

### Study design

This quasi-experimental study is a multicentre prospective, stepped-wedge cluster randomised trial with a continuous recruitment, short exposure design (participants are exposed for a short period with single measurement at a fixed time after the start of their exposure) [10–12].

The nine short-stay geriatric units will be grouped into six clusters (each cluster comprising one to two short stay units), taking into account their patient recruitment capacity and their geographic proximity. The six clusters will be divided into three geographic areas. The order of rollout will be randomised within each geographic area (see Fig. 1). There will be no randomisation between geographic areas.

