### Time steps

The study includes seven time steps (T0 to T6) with a 2-month period between steps. All clusters will start with the control situation (no care transition program) at the beginning of the study. At each time step, a new cluster will cross over from the control situation to the implementation situation. Each cluster will start the implementation of the program at a different time step. At T7, all clusters (and hence all hospitals) will have received the care transition program.

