### Data analysis

Data analysis will be performed by the data management and analysis centre. The analyses will be carried out with the latest version of the R software environment. The lme4 package will be used to implement the generalised linear mixed-effects models. An intention-to-treat analysis will be performed at the cluster level, after the end of the last step (T7).

All of the characteristics collected will be subjected to a descriptive analysis. The comparability of the patients (between the intervention group and the control group, overall, at each time period and within each unit) will be verified.

The univariate analysis will consist in quantifying and testing the effect of the intervention on the proportion of patients undergoing an unscheduled rehospitalisation or an emergency visit.

First, the result criterion will be outlined within each unit and for each period (without the intervention, and then with the intervention). The average proportion will be compared between the two periods using a matched and weighted *t*-test in order to take into account the heterogeneous numbers of patients included in the various units.

As a second step, a mixed-effects logistic regression model with a random effect on the intercept will be used to model the probability of an unscheduled rehospitalisation or emergency visit taking into account the intra-cluster correlation. The effect of the intervention will be quantified using an odds ratio with a 95 % confidence interval. A random effect on the effect of the intervention can be added in order to quantify any heterogeneity of the impact among the units.

The possible evolution of the result criterion over time will be considered by integrating a period variable into the model, enabling the quantification of the effect of each time period with respect to a reference period (the first time period). In the event a tendency is highlighted, the period variable could be introduced into the model as an ordinal variable. This analysis will make it possible to quantify the effect of the intervention after adjusting for a possible time effect. Also, it will be possible to search for an interaction between time and the effect of the intervention.

The analysis can be adjusted on the patient characteristics that are likely to affect the result criterion.

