## Discussion

### Discussion of the study design

A stepped-wedge trial presents methodological advantages [10, 11, 25, 26]. The clusters act as their own controls because they receive both the control and treatment conditions. Therefore, the intervention effect can be estimated from both between- and within-cluster comparisons. In addition, a stepped-wedge trial can take into account the changes in the main criterion over time (fluctuations in unscheduled hospital readmission or emergency visit rate) and enables the quantification of the effect of time on the effectiveness of the intervention (the learning effects).

This type of trial also presents benefits with regard to implementation [10, 11, 25, 26]. It allows the intervention to be administered successively in the participating centres, which can facilitate the organisation of a study in routine practice. The implementation of the intervention at regular time-step intervals also allows for improvement of the intervention or its delivery where necessary before the next implementation step, even if this may introduce differences in the intervention between clusters [10].

Indeed, learning effects may influence the effectiveness of the intervention [26]. First, the TN may become more experienced after enrolling each new cluster, which may lead to differences in the program (albeit small ones) between clusters. Subsequently, this may have an impact on the estimated intervention effect across clusters. Second, clusters will differ in the amount of time spent on the intervention. Eventually, clusters that switch at the first step will be more experienced with the intervention than clusters that switch at later steps. This may also influence the estimated intervention effect. Nonetheless, both types of learning effects can be modelled.

Finally, a stepped-wedge trial makes it possible for each participating centre to benefit from the intervention. This inclusiveness is a motivational factor for taking part in the study, and it also conforms to good ethical practice given that the intervention is expected to do more good than harm.

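### Rollout order is randomised only within geographic areas, but the mixed model has no area term, so an area difference aligned with rollout order can partly leak into the intervention effect

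*Protocol article*

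**What the plan says.** **Randomisation (Study design).** Six clusters are spread over three areas, and chance decides only the sequence inside an area: "The order of rollout will be randomised within each geographic area (see Fig. 1). There will be no randomisation between geographic areas". The text does not say how many clusters each area has, or how the areas' positions in the sequence were chosen. The schedule is in Fig. 1, which is not shown.

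**Crossover (Time steps).** "At each time step, a new cluster will cross over from the control situation to the implementation situation". Each cluster therefore has its own crossover step.

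**Model (Data analysis).** After a matched, weighted t-test of the control and intervention periods, "a mixed-effects logistic regression model with a random effect on the intercept will be used to model the probability" of the outcome. Time enters next: "The possible evolution of the result criterion over time will be considered by integrating a period variable into the model". A random intervention effect is optional. On covariates: "The analysis can be adjusted on the patient characteristics that are likely to affect the result criterion". Geographic area is not named.

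**Use of between-cluster information (Discussion of the study design).** The article counts it as an advantage that "the intervention effect can be estimated from both between- and within-cluster comparisons". It does not add that part of the between-cluster information lies between areas and is not randomised.

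**The concern.** A random intercept treats a cluster's underlying event rate as unrelated to its crossover step. Within an area, randomisation justifies that. Between areas nothing does, because the areas' order was not left to chance.

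With six clusters and a small assumed between-cluster variance, the model draws much of its information from comparing clusters. If the areas that cross early have lower underlying rates than those that cross late, intervention time is over-represented in low-rate areas and the programme looks better than it is. If the gradient runs the other way, a real effect is masked. The sample size calculation uses the same between-area information, so the stated 70 % power partly rests on it under some rollout orders.

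**Working it through.** **1. Reproducing the stated power.** Inputs from the Sample size calculation section: I = 6 clusters, T = 7 periods, 14 patients per cell, 20 % against 10 %, coefficient of variation 0.1, one-sided alpha 5 %. Then tau = 0.1 × 0.20 = 0.02, and the variance of a cell mean is s² = 0.20 × 0.80 / 14 = 0.011429. For one crossover per step, U = 21, W = 91 and V = 91.

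Hussey and Hughes variance:

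Var = I s² (s² + T tau²) / [(IU − W) s² + (U² + ITU − TW − IV) tau²]

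- Numerator: 6 × 0.011429 × (0.011429 + 7 × 0.0004) = 0.0009757
- Denominator: 35 × 0.011429 + 140 × 0.0004 = 0.456
- SE = √0.002140 = 0.0463
- Power = Φ(0.10/0.0463 − 1.645) = 69.7 %

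This matches the stated 70 %.

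**2. Leakage without an area term.** Assumptions, because the document gives none of these: two clusters per area, a constant difference in level between areas, and no true effect. The expected generalised least squares estimate was computed with period effects and a random cluster intercept. The middle area is at 20 % and the first area to cross has the lowest rate. Block order means one area after another (AABBCC), three steps apart means ABCABC, and balanced means ABCCBA. Bias is in percentage points; the planned effect is -10.

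| Area rates | tau | Block | Three steps apart | Balanced |
|---|---|---|---|---|
| 15/20/25 % | 0.02 (plan) | -6.0 | -3.0 | 0 |
| 15/20/25 % | 0.0455 | -4.0 | -2.0 | 0 |
| 15/20/25 % | 0.08 | -2.1 | -1.1 | 0 |
| 18/20/22 % | 0.02 (plan) | -2.4 | -1.2 | 0 |
| 18/20/22 % | 0.0455 | -1.6 | -0.8 | 0 |

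The value 0.0455 is what tau becomes if it absorbs the 15/20/25 % spread: √(0.02² + 0.05² × 2/3). Reversing the gradient reverses the sign. Rates of 20/15/20 % give zero bias in block order. With fixed area terms the bias is 0 in every row.

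There are 6!/(2!·2!·2!) = 90 possible orders of three two-cluster areas. At 15/20/25 % and tau 0.02, 14 of them (16 %) give zero bias. The median absolute bias is 2.3 points and the maximum 6.0.

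**3. Logistic model, simulated.** 14 per cell, residual between-cluster SD 0.02, period-adjusted random-intercept fit, no true effect, 500 to 1,800 runs per scenario. One-sided type I error without the area term:

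- 15/20/25 %, block: about 26 %, mean odds ratio about 0.75
- 18/20/22 %, block: about 10 %
- 15/20/25 %, three steps apart: about 12 %
- 20/15/20 % or 17/23/17 %, block: about 6 %

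Adding area brought it to about 4 to 7 %. With a true fall from 20 % to 10 % and the reversed gradient (25/20/15 %, block), power was 30 % without the area term and 64 % with it.

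**4. Power with the area term, on the plan's inputs.**

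| Order | SE | Power |
|---|---|---|
| Block | 0.0571 | 54.2 % |
| Three steps apart | 0.0484 | 66.3 % |
| Balanced | 0.0463 | 69.7 % |

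**The case against.** A reader might infer that any difference between areas passes into the intervention effect. The documents do not support that. Differences unrelated to rollout order cause essentially no bias, a balanced order causes none even with a gradient, and the random intercept absorbs part of an aligned difference, more so as the estimated cluster variance grows.

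The illustration also rests on assumptions. Block rollout and two clusters per area are not stated. The split matters even for counting allocations: two per area gives 2 × 2 × 2 = 8, whereas a 1/2/3 split would give 1 × 2 × 6 = 12. Rates of 15/20/25 % spread the areas by about 4 points (SD, √(0.05² × 2/3) = 0.041), about twice the plan's total between-cluster SD of 2 points. The 18/20/22 % case is nearer the plan's own input. The mix of hospital types under Setting does not show that areas differ, since their distribution over areas is not given.

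The article labels no single model as primary, and in its first-step matched t-test constant area differences cancel. That test has no adjustment for period, however, so it cannot replace the mixed model.

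It can also be said that covariate lists are usually left to the analysis plan, and that the article openly calls the design quasi-experimental and discloses the restricted randomisation. All this limits the size and certainty of the point. It does not remove it: the article does set out the model and the power method, and neither reflects the randomisation it describes.

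**Conclusion.** The point holds in a limited form. The design randomises within areas only, the described model leaves out that stratum, and non-randomised between-area contrasts therefore enter the estimate. An area difference aligned with rollout order would leak in partly, in favour of the programme or against it.

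Under the assumed block order, an aligned gradient of 5 points per area gives about 4 to 6 points of bias against a planned effect of 10, and one of 2 points per area gives about 1.6 to 2.4. Three steps apart halves this, and a balanced order removes it. Whether this trial is affected at all depends on Fig. 1 and on area rates that the article does not report. The restricted randomisation and the missing area term are certain; the size and direction of any bias are not.

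**What to change.** In Data analysis, add geographic area, the randomisation stratum, as a fixed effect in the mixed model, next to categorical period and intervention. In Sample size calculation, restate the power for that model under the rollout order actually used: on the plan's inputs about 54 % for block order, about 66 % for three steps apart and about 70 % if balanced. These figures assume two clusters per area and need recalculating for any other split.

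The cost is one model line, no patients and no new data, but lower precision when the area order is unbalanced. Fixed cluster effects would also remove constant area differences, at a simulated power of about 63 to 65 % against 78 to 80 % for the random-intercept model without area. Neither option removes time trends that differ between areas, and the text should say so.

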**Fig. 1 Fig1:**
[figure not shown]
Stepped-wedge study with a continuous recruitment, short exposure design. Shaded areas indicate transition program exposure and unshaded areas indicate control exposure

At regular intervals, the clusters will cross over from control to intervention. Each cluster will therefore receive both control and intervention situations consecutively. Data will be collected in all clusters at each time step.

### Time steps

The study includes seven time steps (T0 to T6) with a 2-month period between steps. All clusters will start with the control situation (no care transition program) at the beginning of the study. At each time step, a new cluster will cross over from the control situation to the implementation situation. Each cluster will start the implementation of the program at a different time step. At T7, all clusters (and hence all hospitals) will have received the care transition program.

### Participants

The inclusion criteria are: patient hospitalised for 48 h or more in one of the short-stay geriatrics units participating in the study, aged 75 or older, living at home and with home as the planned place of discharge after admission, and at risk of hospital readmission or emergency visit after discharge. A patient will be considered to be at risk if he meets two or more of the following criteria (derived from the Triage Risk Screening Tool and from the 2013 French recommendations) [5, 13]:Problems in performing activities of daily living (assessed with the Index of Independence in Activities of Daily Living or ADL, and the Instrumental Activities of Daily Living or IADL), excluding the problem of urinary incontinence;One unscheduled hospital admission during the three previous months, or two or more unscheduled hospital admissions during the previous year;A geriatric syndrome such as: two or more falls during the 12 previous months, malnutrition (as defined by the French National Authority for Health), cognitive impairment (degenerative diseases, Alzheimer’s disease, or other dementia), or depression;One or more chronic diseases with high risk of acute decompensation or hospital readmission (i.e., chronic heart failure, chronic respiratory failure, etc.);Polypharmacy (defined as daily intake of five or more drugs); andAn unfavourable social situation (social exclusion, weakness regarding the home helper).

The exclusion criteria are:Patient living in a retirement home (i.e., a nursing home or a residential home for the elderly);Patient hospitalised at home;Patient living at home, but at a distance of 30 km (18 miles) or more from the hospital of index admission; andPatient already included previously in the study (each patient participates in the trial only once).

### Intervention

The hospital-to-home care transition program will be implemented at three times: during the patient’s stay in hospital, on the day of discharge, and for 4 weeks after discharge.*During the patient’s stay in hospital: development of the discharge plan and creation of the transitional care file, and notification of the primary care physician about inpatient care and hospital discharge*The medical team will proceed as usual to deliver a medical and geriatric assessment of the patient and to create a discharge care plan in accordance with the local common ways of care in the unit.The transition nurse (TN) will create a transitional care file including information about the patient (inpatient medical and nursing care plan, medications), the discharge plan, and the contact information of the relevant primary care providers.The TN will notify the patient’s primary care physician (by telephone, email, or fax) regarding the date of discharge to home, any potential medical problems, and the discharge care plan.If necessary, the TN will consider a home assessment visit before the patient is discharged from hospital in order to more accurately assess for aids and contribute to improving the discharge care plan.*The day of hospital discharge (or shortly before discharge): meeting between the transition nurse and the patient to review the follow-up recommendations*The TN will check that medications are prescribed in accordance with the discharge plan, that the patient and his caregiver understand the prescription and its modifications, and that they are informed regarding planned appointments and biological monitoring.The TN will give a handover sheet (intended for the primary care providers) to the patient and his caregiver. This sheet, which will be owned by the patient, will facilitate cross-information transfer.The patient will be given the telephone number of the TN in case he has questions after returning home.*For 4 weeks after hospital discharge: follow-up by telephone and home visit*The TN will follow up on the patient once a week for 4 weeks, through at least two home visits and two telephone calls (Fig. 2).

